## Abstract

**Background:**

Globally, the population aged 65 years and over is increasing and with this growth comes a rising risk of chronic diseases that often require emergency care. Older adults living in Residential Aged Care Facilities (RACFs) have increased healthcare utilisation including visits to Emergency Departments (EDs). EDs are busy, noisy environments poorly suited to meeting the care needs of older adults. Older adults attending EDs often receive delayed and fragmented care, unnecessary procedures and tests and are at greater risk of iatrogenic complications.

The Older Person’s Emergency Network Acute Outreach Service (OPEN AOS) based in Queensland, Australia, is a nurse-led, physician-supported model that provides ED substitution care to older adults living in RACFs. This paper outlines the OPEN AOS study protocol, which comprises three components and uses the integrated Practical, Robust, Implementation, and Sustainability Model (PRISM) and Reach, Effectiveness, Adoption, Implementation and Maintenance (RE-AIM) framework to guide a comprehensive evaluation.

**Methods:**

The study comprises a pragmatic multi-methods design, consisting of three discrete yet related components. Component 1 is a retrospective, quasi-experimental design comparing outcomes for patients seen in the RACF by the OPEN AOS clinical team (intervention group) to standard ambulance attendance in the RACF resulting in transport to ED care (control group) between 1 July 2022 and 30 June 2023. Component 2 is a retrospective economic evaluation of the OPEN AOS model measuring the incremental cost per patient of OPEN AOS care compared to standard ambulance attendance resulting in transport to ED care. Component 3 adopts a prospective qualitative approach to explore and understand the contextual factors influencing implementation with the aim of informing effective delivery and supporting the potential scale and spread of the OPEN AOS model.

**Discussion:**

The OPEN AOS model aims to deliver ED-substitution care in RACFs for older adults. This study will adopt a pragmatic approach to assess both outcomes and implementation processes, utilizing the integrated PRISM and RE-AIM frameworks for comprehensive evaluation. Findings will inform the design of similar models and guide health system decision-making for adopting approaches like the OPEN AOS model.

**Supplementary Information:**

The online version contains supplementary material available at 10.1186/s12877-025-06917-2.

## Background

Globally the sustained growth of the older population poses numerous challenges for both individuals and healthcare systems. By 2030 the world is predicted to have one billion older adults, accounting for 13% of the total population [1]. In Australia, the proportion of people aged 65 years and over will increase from 17% in 2022 to between 25% and 27% in 2071 [2]. As people age, they are more likely to have multiple chronic health conditions that require healthcare [3–5]. Between 2012 and 2022 Australia saw admissions into Residential Aged Care Facilities (RACFs) double [6]. The utilisation of Emergency Departments (EDs) also increased [7]. In 2017-18 patients aged 65 years and older accounted for 21.6% (*n* = 1,731,121) of the 8 million ED presentations and this increased to 23.3% (*n* = 2,105,259) of the 9 million presentations in 2023-24 [8, 9].

A systematic review of qualitative studies by O’Neill et al. (2015) highlights the complex factors influencing ED transfer decisions from RACFs. Key factors included poor care planning, limited access to timely medical reviews, inadequate staffing within RACFs, medico-legal risk mitigation and conflict among stakeholders regarding the necessity of transfer [10]. While the ED is uniquely designed to provide assessment and diagnostics for the prevention, treatment and management of the critically ill or injured, it is a suboptimal environment for the provision of care to the frail, older adult [11]. Older patients often have long lengths of ED stays [12, 13], and if from an RACF, can undergo unnecessary investigations and invasive interventions with an increased risk of developing iatrogenic complications if admitted [14]. Older adults often experience longer wait times to be offloaded from an ambulance and are more likely to exceed the benchmarked wait time be to seen by an emergency doctor [15–18].

Existing policies set standards of care for older people in EDs [19] and evidence from both ED-focused models [20–22] and supportive care models – locally and internationally – shows that while specialized ED care is important, transportation of many older patients to the ED could be avoided if supportive care models were available. These care models include enhanced primary care for improved surveillance and management of illness; advanced care directives; palliative care; and clinical pathways for specific disease management [23–27].

However, the coordination and continuity of care for the older adult remains paramount [28, 29]. There are key considerations when providing acute care to an individual in the RACF such as: ascertaining their goals of care; treatment beneficence; non-maleficence (e.g. avoiding futile treatment); and understanding the capacity to diagnose and manage care safely in the home [30]. Various medical problems can be effectively treated and managed in the resident’s home such as urinary tract infections and falls with minor injuries including skin tears or simple lacerations [31]. A recent systematic review of ED transfers determined up to 55% were potentially avoidable, meaning the resident was safe to remain in their home utilising alternative care pathways [32]. Additionally, some evidence suggests that RACF residents and their families have a general preference for treatment to be provided in their home environment [33].

A systematic review of 15 observational studies evaluating acute outreach models of care to people living in RACFs on ED transfer prevention, hospitalisation, safety, cost-effectiveness and experiences [34] highlighted the absence of evidence. The authors recommended that future cluster-randomised or quasi-experimental studies be undertaken to assess the effectiveness and safety of these new outreach models [34].

To support the provision of emergency care for residents in RACFs in Queensland Australia, a novel acute ED substitution outreach model called OPEN AOS (Older Persons Emergency Network Acute Outreach Service) was established. The overarching aim of this study is to evaluate the implementation and outcomes of this ED outreach model. This paper describes the protocol for the evaluation of the OPEN AOS model.

## Methods

### Study aims

The aims of the OPEN AOS model evaluation are to:

Describe and compare the effectiveness and safety of the OPEN AOS model with standard ambulance attendance resulting in transport to ED care (standard care).Conduct an economic evaluation of the OPEN AOS model; and.Explore and understand the contextual factors influencing implementation to inform delivery and support potential scale and spread of the OPEN AOS model.

## Setting

The study is set in the Metro North Hospital and Health Service (MNHHS) district in south-east Queensland, Australia [35]. In 2024, the MNHHS region had 87 RACFs (85 non-government) with 9417 RACF beds. The district is serviced by five public hospitals; four are classified as large or very large and one is classified as small. The EDs within each of the five hospitals vary in their level of service capability and capacity [36, 37].

## Control: standard ambulance model of care

In Queensland, prehospital emergency care is provided by the Queensland Ambulance Service (QAS), a single, state-wide, government-funded emergency ambulance service. Like other Australian and international ambulance services, primary triage of calls is completed by a non-clinical Emergency Medical Dispatcher to determine the nature and type of incident, and the response time criticality. All incidents are assigned as either: emergency (potentially life threatening – immediate response with lights and siren); urgent (acute – immediate response with no lights and siren); or non-emergency (time critical scheduled conveyance or routine) response. Incidents are subsequently assigned either an immediate dispatch response or are transferred for clinical review performed by a multidisciplinary team of experienced paramedics, medical practitioners, mental health clinicians, social workers and Registered Nurses (RNs). Following clinical review, patients are assigned the most appropriate health response, which may include a dispatch response or referral to equivalent care pathway, and/or virtual care (i.e., health care consultation provided via telehealth platform run by RNs and medical practitioners). The majority of QAS patients (over one million annually) are transported from the scene [38], and approximately 90.0% of transports are to public hospital EDs [39].

## Intervention: the OPEN AOS model

The OPEN AOS model provides emergency substitution care to older adults residing in RACFs located within the MNHHS catchment area. Nurse-led and physician supported, OPEN AOS commenced in January 2022 and became fully operational by June 2022. The service is based in office space adjacent to a MNHHS hospital and operates 12 h per day between the hours of 08:00–20:00, Monday to Sunday. The service aims to (i) decrease the time to treating emergency clinician and (ii) reduce the number of avoidable ambulance transports to ED for older adults living in RACFs. The OPEN AOS model is staffed by 3.0 full-time equivalent (FTE) Nurse Practitioners^1^ (NP); 1.0 FTE NP candidates (NPC)^2^; and 1.8 FTE RNs^3^ [40, 41]. The model is supported by 1.4 FTE Senior Medical Officers (SMO)^4^ [42, 43] and 0.8 FTE Senior Pharmacists 5 [44]. The service is funded by MNHHS. Detailed descriptions of the responsibilities of the OPEN AOS clinical roles are provided in Additional file 1.

Patients of OPEN AOS are older adults residing in RACFs experiencing acute illnesses or injuries. OPEN AOS clinicians provide emergency substitution care via telehealth or in person. Referrals originate from the ambulance service (either from paramedics attending the patient at the RACF or following secondary telephone triage by experienced ambulance service clinicians), General Practitioners (GPs), RACF staff and other local teams providing specialist sub-acute RACF consulting services. Each referral is reviewed by an OPEN AOS clinician who triages the case and determines suitability for OPEN AOS care. Patients not meeting eligibility criteria for the OPEN AOS remain in the care of ambulance services for secondary triage and receive standard clinical review, consideration of referral pathways and standard ambulance attendance.

## Study design

This pragmatic multi-methods study comprises three discrete but related components: concurrent retrospective quantitative data collection for Components 1 and 2, and prospective qualitative data collection for Component 3. The approach to quantitative and qualitative data collection enables a comprehensive examination of the model’s effectiveness and real-world application. Given the multi-methods design, integration of quantitative and qualitative data through triangulation will not be undertaken. The design is underpinned by the integrated Practical, Robust, Implementation and Sustainability Model (PRISM) and Reach, Effectiveness, Adoption, Implementation and Maintenance (RE-AIM) framework [45]. PRISM will support the identification and description of contextual factors impacting RE-AIM outcomes [45]. This study has been reviewed and approved by the Metro North Human Research Ethics Committee (HREC) B (ECOO168), approval number 102,923. Data storage, retention and disposal will be conducted in accordance with the National Health and Medical Research Council (NHMRC) guidelines [46].

Three components are planned to address the following research questions:

*Component 1*

To what extent (if any) do patient characteristics (such as age, sex, and diagnostic classification^6^) and outcomes differ between OPEN AOS care and standard care (i.e. ambulance attendance with transport to ED care)?Specifically:

4.Primary Outcome: Time to be seen by treating clinician, defined as the amount of time in minutes from the initial contact with QAS to the time seen by either (i) the OPEN AOS clinician (intervention group) or (ii) the ED medical officer (control group).5.Secondary Outcomes:6.Length of care episode, defined as the amount of time in hours from initial contact with QAS to discharge of care.7.Ambulance transport to ED care: defined as the proportion of OPEN AOS patients requiring transport to ED for definitive care.8.ED re-presentation for any cause within 48 h and 28 days of discharge.9.Death within 48 h of discharge.10.Clinical incident^7^ [47] data, defined as clinical incidents that are reported by MNHHS staff that occur within 48 h of discharge.

*Component 2*

Compared to standard care, what is the incremental cost (saving) per person of the OPEN AOS model? 

*Component 3*

How do contextual factors influence implementation and potential future scale and spread of the OPEN AOS model?

Detailed explanations of outcomes to be measured across all three components are presented in Additional file 2.

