### Component 1: Comparison of OPEN AOS model to standard care

#### Design

Component 1 is a retrospective, quasi-experimental design. This design was considered to be the most appropriate given the availability of pre-existing data and feasibility [48, 49]. Individual and treatment characteristics and outcomes for patients treated by OPEN AOS (intervention group) or received standard care (control group) will be compared. Figure 1 illustrates the potential patient pathways from the RACF, depicting management either by OPEN AOS or via ambulance attendance with transport to the emergency department (ED).

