### Samples

In the 12-month study period from 1 July 2022 to 30 June 2023, approximately 7600 ED presentations from RACFs arrived by ambulance to district’s ED sites. During that same period, 735 patients were treated by OPEN AOS during their operational hours (08:00–20:00) Monday to Sunday. Patients treated in the Intervention group will be matched with up to three randomly selected control group patients without replacement with matching on age (+/- 5 years), and exact matching on sex and diagnostic classification section (or chapter if diagnoses are uncommon) as per the International Classification of Diseases, 10th Revision Australian Modification (ICD-10-AM) using the ‘R’ package Matching: Multivariate and Propensity Score Matching with Balance Optimization [50]. Groups sizes of 351 for the intervention group and 1053 for the control group will achieve 90% power to reject the null hypothesis of no effect on the time to be seen by treating clinician when there is a Cohen’s d small effect size of 0.2 using a two-sided, two-sample test assuming equal variance and an alpha of 5% [51].

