### Data analysis

For our analysis, the comparison of interest is between the intervention and control groups. Re-presentations by patients in either group are not considered as independent events and will be excluded from analyses, however the number of re-presentations during the study period will be noted for the OPEN AOS group. Categorical data will be presented as frequency and percentages, while continuous data will be reported as mean with standard deviation or median with interquartile ranges, depending on the distribution of the data. Categorical data will be analysed using the Pearson Chi-squared test or Fisher’s exact test, and continuous variables using the Student t-test or Mann-Whitney U test. Time to treating emergency clinician and time to discharge from the episode of care will be examined using a generalised linear model or parametric regression model if events are censored e.g., death of a patient. ED re-presentation and mortality will be examined using logistic regression if there are sufficient events. All regression models will be multivariable with fixed effects for triage score, weekend presentation, season, and ambulance referral time. The inclusion of Charlson Comorbidity Index [52] in regression analyses will depend on the extent of missing data. Component 1 will be reported in accordance with the Enhancing the QUAlity and Transparency Of health Research (EQUATOR) guidelines for reporting non-randomised studies [53].

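### Component 1 asks how age, sex and diagnosis differ between OPEN AOS and standard care, but matches its controls on these three variables and plans no pre-matching comparison

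*Protocol article*

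**What the plan says.** Four places in the protocol article bear on this point.

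- **Study design, Component 1 question.** It asks to what extent "do patient characteristics (such as age, sex, and diagnostic classification" and outcomes differ between OPEN AOS care and standard care. The three characteristics are given as examples.
- **Component 1, Design.** "Individual and treatment characteristics and outcomes for patients treated by OPEN AOS (intervention group) or received standard care (control group) will be compared".
- **Component 1, Samples.** Controls are selected by "matching on age (+/- 5 years), and exact matching on sex and diagnostic classification section (or chapter if diagnoses are uncommon"). Each intervention patient gets as many as three, drawn at random, and no control is used twice. The planned sizes are 351 intervention and 1053 control patients.
- **Component 1, Data analysis.** "For our analysis, the comparison of interest is between the intervention and control groups". For the tests, "Categorical data will be analysed using the Pearson Chi-squared test or Fisher’s exact test", with the t-test or Mann-Whitney test for continuous variables.

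The Inclusion criteria define controls more broadly, as eligible residents transported to a district ED in the same hours and year. No section says that OPEN AOS patients will be compared with that whole group before matching.

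**The concern.** The three characteristics named in the question are the three matching variables. Matching makes the groups alike on these variables whatever the true difference between the services' patients. A table of age, sex and diagnosis in the matched sample describes the sampling rule, not who each service sees.

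The answer matters because the two services probably see different residents: under the OPEN AOS model, a clinician reviews each referral and decides whether it is suitable. A reader of the results may want to know how OPEN AOS patients compare with the residents behind the roughly 7600 ambulance arrivals. If the matched table is offered as the answer, similarity imposed by design could be taken as a finding about case mix.

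**Working it through.** **1. Which control group is sized.** With 3 controls per intervention patient, d = 0.2, two-sided alpha 5% and 90% power:

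n(intervention) = (1 + 1/3) × (1.960 + 1.282)² / 0.2² = 1.333 × 10.51 / 0.04 ≈ 350.3, rounded up to 351; controls 3 × 351 = 1053.

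Power at 351 and 1053 is 90.06% by the normal approximation and 90.02% by the noncentral t. The stated figure reproduces. Because 1053 is exactly 3 × 351, the control group that is sized is the matched set.

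**2. Sex and diagnosis after exact matching.** Let x be 1 if a patient has the attribute (female, or a given diagnosis section) and 0 otherwise. Let intervention patient i have k_i matched controls, all with the same x. Over m matched sets, the unweighted difference is

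control proportion − intervention proportion = Σk_i x_i / Σk_i − Σx_i / m = Cov(k, x) / mean(k).

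If every set has the same number of controls, or sets are weighted equally, this is exactly zero for any true difference. With up to three controls and no weighting it is non-zero only if set size varies with the attribute. That remainder reflects how many matches were available, not the difference in case mix.

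**3. Age.** Each control lies within 5 years of its intervention patient, so the matched mean difference cannot exceed 5 years. Random choice within that window removes most, but not all, of a smaller true difference.

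**4. Illustration.** The article gives no distributions, so these inputs are assumptions: 351 intervention patients, 4000 eligible controls, age SD 7.5 years, 70% v 60% female, eight diagnosis groups with a largest gap of about 15 points, up to three random matches without replacement, 60 replicates, unweighted comparison.

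| Characteristic | Before matching | After matching | Age test significant (5%) |
|---|---|---|---|
| Female | about 10 points | 0.0 points | – |
| Largest diagnosis gap | about 15 points | at most 0.1 points | – |
| Mean age, true gap 2 years | 2.0 years | 0.4 years | 0% of runs |
| Mean age, true gap 4 years | 4.0 years | 0.8 years | 35% of runs |

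About one fifth of the age gap remains (0.391 / 2.012 = 0.19; 0.795 / 3.957 = 0.20). This fraction depends on the assumed age spread.

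**5. Sensitivity to sample size and unmatched patients.** With all 735 treated patients, 4000 controls and a 2-year age gap, the unweighted residuals are about 0.3 points for diagnosis and 0.1 points or less for sex. About 5 to 7% of intervention patients find no control, depending on the run. If they stay in the intervention column, the largest diagnosis gap is about 3.5 to 3.9 points, still far from 15.

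**The case against.** The strongest reply is that the article uses control group in two senses. Samples speaks of control patients from whom matches are drawn, which is the pool defined under Inclusion criteria. On that reading, the comparison of characteristics could cover the whole pool, with the matched subset kept for the outcome models. Data analysis does not exclude this, and an article often leaves a before-and-after matching table to a fuller document. The ambiguity is real. But the group that is sized is the matched set, and no section assigns the characteristics question to the unmatched pool. The article does more than omit a detail: it poses a question about three variables and specifies a sample that cannot answer it.

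The reply is right about scope. The three variables are examples; comorbidity, triage score, weekend, season and referral time are not matched and can still be compared. No patient characteristic is a primary or secondary outcome. The Limitations section already warns of selection bias and baseline differences.

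A reader might infer that the comparison is forced to show exactly no difference, or that the tests have no power. The documents do not support that. Age is matched only within 5 years, and a 4-year gap still reached significance in 35% of illustrative runs. Diagnosis can differ below section level, or within a chapter where chapters are used. Unequal numbers of controls leave small imbalances.

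**Conclusion.** The point holds in limited form. For age, sex and diagnostic classification, the matched sample cannot show how OPEN AOS and transported patients differ: sex and matched-level diagnosis are close to balanced by construction, and age differences are strongly shrunk. The conclusion for sex and diagnosis follows from the matching rule and does not depend on the assumed distributions. The small residuals, the age remainder of about one fifth and the unmatched share do depend on them.

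It would be wrong to infer that matching harms the study's main results. The outcome comparisons, the sample size and the comparison of unmatched characteristics stand. The defect lies in using, or appearing to use, the outcome sample for a question about case mix. It should be corrected, but it does not threaten the primary analysis.

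**What to change.** In Samples and Data analysis, name two populations.

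1. **Before matching:** all eligible OPEN AOS patients and all eligible transported residents under the inclusion and exclusion criteria. Answer the question for age, sex and diagnostic classification here, with differences and 95% confidence intervals or standardised differences.
2. **Matched sample:** use it for the outcome comparisons. Show its age, sex and diagnosis only as a balance check, without significance tests.

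Report the number of intervention patients left without a match, and use control group in one sense throughout. If the team does not want the first comparison, the alternative is to remove the three matched variables from the research question.

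The cost is a sentence or two of text and one descriptive table. The eligible pool has to be extracted to draw the matches, so no new data are needed and the power calculation is unchanged.

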### Inclusion criteria

Intervention: Adults aged 65 years or older who are permanent residents of RACFs situated within the MNHHS district geographical catchment area, with acute care needs and who were referred by the ambulance service to OPEN AOS between 08:00 and 20:00, Monday to Sunday, from 1 July 2022 to 30 June 2023. Patients can receive treatment by OPEN AOS on more than one occasion within the study period.

Control: Adults aged 65 years or older who are permanent residents of RACFs situated within the MNHHS district geographical catchment area, who received standard ambulance attendance and transport to a MNHHS ED between 08:00 and 20:00, Monday to Sunday, from 1 July 2022 to 30 June 2023. Only the first presentation for each patient within the study period will be examined.

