### Future implications

This study will provide ED clinicians and policy makers with evidence on the impact, translatability and cost efficiency of the OPEN AOS model within one hospital and health service in South-East Queensland, Australia. Findings will inform local model refinements and guide future resource allocation decisions. Importantly, this evidence will add to the body of knowledge regarding emergency care for older vulnerable adults residing in RACFs. This study will provide valuable information regarding this emergency outreach model’s capacity to deliver timely care and reduce unnecessary transport of older adults to ED. Furthermore, the identification of barriers and enablers to implement and scale effective emergency substitution models can guide future endeavours to strengthen emergency care for older adults.

Findings from this study have the potential to inform national and international frameworks aimed at improving access to and quality of emergency care for older adults. These insights may guide adaptation of similar models in other jurisdictions and support the development of patient-centred approaches to emergency care for vulnerable older populations. As the global community adapts to an aging population, continued efforts to optimise care for older adults in their place of residence through the use of alternative care options (such as OPEN AOS) are required.

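### Controls are selected for having been transported to ED, so the transport outcome can describe OPEN AOS patients but cannot show a reduction against usual ambulance care

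*Protocol article*

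**What the plan says.** Under Study design, the Component 1 research question asks how far patient characteristics and outcomes differ between OPEN AOS care and standard care. One of the secondary outcomes listed beneath it is "Ambulance transport to ED care: defined as the proportion of OPEN AOS patients requiring transport to ED for definitive care". It is defined for the intervention group only.

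The two groups enter by different routes (Inclusion criteria):

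- Controls are residents "who received standard ambulance attendance and transport to a MNHHS ED between 08:00 and 20:00, Monday to Sunday".
- Intervention patients are residents "who were referred by the ambulance service to OPEN AOS between 08:00 and 20:00, Monday to Sunday", whether or not they are later taken to an ED.

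The section on the standard ambulance model describes usual care more broadly than this control group. After clinical review a patient receives a response "which may include a dispatch response or referral to equivalent care pathway, and/or virtual care". On transport it says: "The majority of QAS patients (over one million annually) are transported from the scene".

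The section on the OPEN AOS model gives fewer avoidable ambulance transports as one of the service's two aims. Future implications says the study will provide information on the model's "capacity to deliver timely care and reduce unnecessary transport of older adults to ED". The Component 2 data analysis section costs standard care as an ambulance attendance plus an ED presentation, and scales avoided ED presentations and savings to all 87 facilities.

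**The concern.** A reduction in transport needs two quantities: the share of patients transported under OPEN AOS, and the share of comparable patients who would have been transported without it. The control group cannot supply the second, because a usual-care patient who was not transported cannot become a control. Placing the outcome under a between-group question, together with the statement in Future implications, invites a reader to set the OPEN AOS figure against an implied 100%.

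At stake is what the study may conclude on one of the service's two stated aims. The same implied 100% can also carry into the economic model, through the number of ED presentations counted as avoided.

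**Working it through.** **The plan's own figures.** The article gives no figure for transport. Its one power statement (Samples) concerns the primary outcome: 351 and 1053 patients, standardised effect 0.2, two-sided 5%. It reproduces, with a noncentral t power of 0.900, and 351 is the smallest intervention group that reaches 90% at 1:3. The present point does not depend on it.

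**Definitions**

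- p = proportion of OPEN AOS patients transported to ED. It can be estimated from the study and is free to lie between 0 and 1.
- q = proportion of comparable residents transported under usual ambulance care. The article gives no value.
- c = proportion transported in the control group. By the inclusion criterion c = 1, with no sampling variation.

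**Step 1. What the design returns.** Setting the groups side by side gives c − p = 1 − p. This cannot be negative, whatever the true effect.

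**Step 2. What a reduction would be.** The quantity of interest is q − p.

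**Step 3. The gap.** (1 − p) − (q − p) = 1 − q. The overstatement does not depend on p. It is zero only if every OPEN AOS patient would otherwise have been transported.

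**Step 4. Illustration, with p and q both assumed.** Take p = 0.20 and, for scale only, the 735 patients treated by OPEN AOS in the study period (Samples). The analysed number will differ, because patients not referred by the ambulance service are excluded.

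| Assumed q | Apparent reduction 1 − p | Reduction q − p | Overstatement 1 − q | 735 × (1 − p) | 735 × (q − p) |
|---|---|---|---|---|---|
| 1.0 | 0.80 | 0.80 | 0 | 588 | 588 |
| 0.9 | 0.80 | 0.70 | 0.10 | 588 | 514.5 |
| 0.7 | 0.80 | 0.50 | 0.30 | 588 | 367.5 |
| 0.5 | 0.80 | 0.30 | 0.50 | 588 | 220.5 |

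**Step 5. Can the analysis recover q?** No. Matching is on age, sex and diagnosis. The regression covariates are triage score, weekend, season and referral time, with comorbidity if the data allow. These act only on patients who were sampled, and usual-care patients who were not transported are absent.

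**The case against.** The strongest reply is that the protocol plans no between-group comparison of transport. The outcome is defined for OPEN AOS patients alone. The Component 1 data analysis section names time to clinician, time to discharge, re-presentation and mortality for modelling, but not transport, and no control figure of 100% appears anywhere. Future implications promises information on capacity, not an estimate against what the ambulance service would have done. The share of referred patients who still need an ED is legitimate information of that kind. The comparator is declared openly throughout, and Limitations says that selection bias and unmeasured confounding restrict causal inference.

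Most of this stands. A reader might infer that the authors intend to test or claim a transport reduction against 100%; the text does not say so. A reader might also infer that the one-group definition was adopted because controls are all transported. That is plausible, but the article gives no reason. Nor can a size be read from the article: the statement that most ambulance patients are transported covers all the service's patients, and the alternative pathways it mentions may include OPEN AOS itself. Hence q is an assumption throughout.

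What does not stand is that the general caveat in Limitations covers the point. It speaks of baseline differences and confounding, not of controls selected on the outcome in question. The outcome also still sits under a question that it cannot answer.

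A new comparator cohort drawn from ambulance records might look like the obvious remedy. It is harder than it seems. Residents are identified on arrival at ED, no listed source clearly supplies a diagnosis for those not transported, and callers not referred to OPEN AOS differ from those referred because of clinical judgement at triage.

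**Conclusion.** The point holds as a limit on interpretation. By the inclusion criteria the control transport proportion is 100%, so the transport outcome describes how often OPEN AOS patients still go to ED and nothing more. It cannot show a reduction against usual ambulance care. Reading 1 − p as the reduction overstates it by 1 − q: 10 to 50 percentage points for an assumed q of 0.9 to 0.5, and nothing if q is 1. The only firm inputs are the inclusion criteria and the outcome definition.

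Two stronger readings are not supported. One is that OPEN AOS fails to reduce transports; the design is silent on that in either direction. The other is that the primary comparison is undermined by this point. The argument here concerns the transport outcome and, through the implied 100%, the count of avoided ED presentations in Component 2.

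**What to change.** 1. In Study design, take the transport outcome out of the list under the between-group question and label it a descriptive one-group transfer rate for OPEN AOS patients, reported with a 95% CI.
2. In Limitations and Future implications, state that controls were selected on having been transported, so the design cannot estimate a reduction in transport.
3. In Component 2, where avoided ED presentations are modelled, vary the assumed usual-care transport probability below 100% in the one-way and probabilistic sensitivity analyses already planned.
4. Optional and exploratory: from the ambulance dispatch and clinical data already listed as a source, describe the proportion transported among all in-hours incidents at catchment facilities that were not triaged as emergency, urgent as well as non-emergency, transported or not. Do this only if such incidents can be identified, and report it as subject to confounding by indication.

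Items 1 and 2 are wording and cost nothing. Item 3 adds one parameter to a planned analysis. Item 4 needs a wider extract and a way of identifying residents that does not depend on ED arrival, so it should not be a condition of the other three.
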